The TTS counselor also inquires about patients’ plan regarding their smoking after hospital discharge. If a patient clearly is not motivated to quit, contact time with the TTS counselor is typically less than five minutes. These patients are not referred for study recruitment. Patients who plan to stay quit or try to quit after discharge receive a median of 20 minutes of bedside counseling to create a personalized quit plan. The session includes a specific smoking cessation medication recommendation, tips on how to abstain from smoking after discharge, and information about counseling services available after discharge. At the end of the counseling session, the TTS counselor offers smokers who plan to quit after discharge and meet inclusion criteria information about the study and refers them to research staff for recruitment. Research staff visit the smoker in the hospital to describe the study, assess eligibility, obtain informed consent, collect baseline data, and assign the patient to a study arm. Research staff also prioritize the recruitment of patients with HIV infection on any day when such a patient is referred to them. The participant’s primary care physician is notified about the trial and about any medications prescribed with a note in the electronic health record or by fax.

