### Assignment to treatment group

At each study site participants are randomly assigned to either Standard Care or Sustained Care by research staff in a 1:1 fashion using permuted blocks of 8. Randomization is stratified into five groups: four strata were created by crossing daily cigarette consumption (<10 versus ≥10 cigarettes per day) with admitting service (cardiac vs. non cardiac), and a fifth stratum was created for HIV-infected patients. A series of sealed manila envelopes was created for each stratum, with the randomization ID on the outside of the envelope and the study arm assignment inside the envelope. The research assistant informs the participant and initiates the protocol for the assigned study arm. The study is not blinded to participants or to research staff, but enrollment and follow up activities are conducted by research staff members not involved with recruitment.

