***Items in bold italics were only in Helping HAND 2.***

All other measures were used in both Helping HAND 1 and 2.

^1^Asked only of participants who self reported continuous abstinence at 6 month follow-up.

*Demographic factors*: sex, age, race/ethnicity, educational attainment, employment status, marital/partner status, and type of housing are collected by participant interview and chart review at baseline.

*Tobacco use history* includes cigarettes per day, use of other tobacco products, and use of electronic cigarettes in the month prior to admission, number of years smoking, prior quit attempt (yes/no), presence of a smoker in the household, and home smoking policy. *Prior tobacco treatment* is assessed at baseline by asking about previous use of NRT, bupropion, varenicline, telephone counseling support, and in-person counseling support. *Nicotine dependence* is assessed by asking time to first cigarette of the day.

*Intention to quit* upon discharge is assessed with the item described in Table 2. Perceived *importance* of quitting and perceived *confidence* in ability to quit are assessed with 5-point Likert-type scales ranging from “not at all” to “very” at baseline. Confidence is reassessed at each follow-up.

*Alcohol use* in the past year is assessed at baseline and 6 months using the three-item Alcohol Use Disorder Identification Test—Consumption [30]. *Other substance use* is assessed at baseline by asking about any use in the past year of marijuana, cocaine, crack, stimulants, and opioids. Injection drug use is assessed by asking about participants’ lifetime use and their use within the past year.

*Anxiety and depression symptoms* are assessed at baseline and at each follow-up using the Patient Health Quessionaire-4, a 4-item inventory rated on a 4-point Likert scale ranging from “not at all” to “nearly every day” [31]. The first two questions measure anxiety symptoms and the latter two measure depression symptoms. Scores range from 0-12, with higher scores indicating more symptoms.

*Quality of life* is measured at baseline and 6-month follow-up using the EQ-5D instrument [32]. It assesses quality of life on a 5-point Likert scale with answers ranging from “no problems” to “unable” and “not at all” to “extremely”. The questions range from physical mobility (problems walking, washing, dressing, pain, and discomfort) to psychological (feeling anxious or depressed).

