### Data analysis

A total sample of 1350 was planned to detect a difference of 4.8% (12.8% vs. 8.0%) in the primary outcome measure, validated 7-day tobacco abstinence at 6-month follow-up, with 80% power and a 2-tailed type I error rate of .05. Analysis of study data will use an intention-to-treat approach. In the primary analysis, subjects lost to follow-up due to all circumstances will be coded as smokers for smoking status outcomes. A sensitivity analysis will be conducted based on different assumptions on missing data [33]. Multiple imputation techniques will also be used to take into account uncertainty due to missing data.

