#### Primary outcome

The primary smoking outcome is biochemically-validated 7-day point prevalence abstinence from all tobacco products at 6 month follow-up. For the analysis, Cochran-Mantel-Haenzel tests will first be used to determine whether intervention effects are consistent across the 3 study sites. Logistic regression analyses will be used to compare the effect of study arm on the primary outcome measure, adjusting for study site.

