#### Secondary outcomes

For all outcomes measured at 1, 3, and 6 months, cross-sectional analyses will be used to compare between study groups. Secondarily, a longitudinal analysis using Generalized Estimating Equations (GEE) techniques will be conducted to assess the overall impact of Sustained Care by including data from all follow-up times. Similar to the primary outcome, regression models will be used to compare treatment group adjusting for site and any important confounders; these will be logistic regression for dichotomized outcomes (e.g. self-reported abstinence, any counseling/medication use), and Poisson regression for the number of event outcomes (e.g. number of counseling contacts, number of emergency room visits, number of hospital readmissions). Survival analysis techniques will be used to analyze the duration-related outcome variables (self-reported duration of continuous abstinence and duration of post-discharge medication use). Kaplan-Meier curves will be used to estimate the median duration of tobacco abstinence and medication use. Cox proportional hazard models will examine intervention effects adjusting for potential confounding factors.

*Cost-effectiveness* will be assessed using cost per quit as the main outcome in order to compare our results with other published studies [22,34,35]. The incremental costs per quit are estimated as follows: (Total costs of Sustained Care – Total costs for Standard Care)/(Total successful quits at six months for Sustained Care – Total successful quits at six months for Standard Care) where successful quits are defined according to our primary outcome of 7-day point prevalence abstinence. The major costs tracked in the study are as follows: (1) initial counselor assessment pre-discharge, which includes counselor chart review, counseling, and medication recommendations; (2) Quit Coach medication assessment and cessation support post-discharge; (3) IVR service; and (4) medication costs, including dispensing and delivery. For both study arms, we will track the portion of counseling and medication costs paid for by participants out of pocket and/or by insurance.

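### The primary logistic model adjusts for site only; a short pre-specified list of baseline covariates already collected would add a modest amount of power at almost no cost

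*Protocol article*

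**What the plan says.** All references are to the protocol article.

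- **Primary model** (Primary outcome section): "Logistic regression analyses will be used to compare the effect of study arm on the primary outcome measure, adjusting for study site". Site is the only covariate named.
- **Order of events** (Recruitment section): research staff "obtain informed consent, collect baseline data, and assign the patient to a study arm". The Assessments section places the baseline survey directly after consent.
- **Candidate covariates** (Table 3 and Participant surveys): nicotine dependence "is assessed by asking time to first cigarette of the day", and confidence is rated at baseline on a five-point scale. Intention is recorded with the eligibility item in Table 2. Only its two most committed answers allow enrolment, so it has two levels in the trial.
- **Randomisation** (Assignment to treatment group): at each site, allocation is "in a 1:1 fashion using permuted blocks of 8" within five strata. Four cross daily cigarette consumption with cardiac or non-cardiac service; the fifth is for HIV-infected patients. The stated primary model does not contain these factors either.
- **Secondary models** (Secondary outcomes section): introduced as resembling the primary analysis, but "regression models will be used to compare treatment group adjusting for site and any important confounders". The confounders are not named.
- **Planning target** (Data analysis section): "A total sample of 1350 was planned to detect a difference of 4.8% (12.8% vs. 8.0%) in the primary outcome measure", "with 80% power and a 2-tailed type I error rate of .05".

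**The concern.** In a randomised trial, adjusting for baseline measures that predict the outcome raises the power of the treatment test, and fixing the list in advance keeps the analysis free of choice. The protocol already treats these measures as relevant to quitting. Intention decides eligibility, time to first cigarette guides the choice of medication, and low confidence prompts a recommendation to speak to a counsellor. None of them enters the primary comparison.

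The stake is modest: some power is left unused on an outcome expected in roughly one participant in ten. Enrolment has closed at 1,359, so recruitment can no longer add power, whereas the analysis can. A second, smaller matter is the scale of the result. The trial was planned on a 4.8-point risk difference, but the named model yields an odds ratio.

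**Working it through.** **1. Reproduce the planned sample size.** Inputs from the Data analysis section: p0 = 0.080, p1 = 0.128, d = 0.048, two-sided alpha 0.05, power 80%. Mean rate = 0.104.

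n per arm, pooled formula = [1.960 × √(2 × 0.104 × 0.896) + 0.842 × √(0.080 × 0.920 + 0.128 × 0.872)]² / 0.048² = (0.846 + 0.362)² / 0.002304 ≈ 633.7, so 634 (total 1268).

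With continuity correction: (633.7 / 4) × [1 + √(1 + 4 / (633.7 × 0.048))]² ≈ 674.7, so 675 per arm and **1350 in total**, an exact match. Without the correction, 675 per arm gives 82.4% power. The plan reaches its target with no covariates.

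**2. Approximate gain from adjustment.** If baseline covariates explain a share R² of outcome variance, effective N = 1350 / (1 − R²), and the interval for a marginal effect narrows by 1 − √(1 − R²). The article gives no R²; the range below is assumed.

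| Assumed R² | Effective N | Power, continuity-corrected (base 80.0%) | Power, uncorrected (base 82.4%) | Narrowing of marginal interval |
|---|---|---|---|---|
| 0.02 | 1378 | 80.8% | 83.2% | 1.0% |
| 0.05 | 1421 | 82.0% | 84.3% | 2.5% |
| 0.08 | 1467 | 83.2% | 85.4% | 4.1% |
| 0.10 | 1500 | 84.0% | 86.2% | 5.1% |

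**3. Simulation with one combined prognostic score.** 675 per arm, marginal rates held at 8.0% and 12.8%, 4,000 runs per setting. The Wald test from an arm-only logistic model is compared with one that adds the score and two pure-noise covariates. Site was not simulated.

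| Assumed odds ratio per SD of score | Control-arm R² | Conditional odds ratio for arm | Power unadjusted | Power adjusted |
|---|---|---|---|---|
| 1.00 (not prognostic) | 0 | 1.69 | 81.4% | 81.5% |
| 1.35 | 0.007 | 1.70 | 82.8% | 83.4% |
| 1.65 | 0.019 | 1.71 | 83.2% | 83.6% |
| 2.12 | 0.044 | 1.74 | 82.6% | 84.6% |
| 2.72 | 0.080 | 1.78 | 82.9% | 86.3% |

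The Monte Carlo standard error is about 0.6 points per estimate. Both tests use the same simulated data, so the differences are steadier than the levels. The prognostic settings gain about 0.4 to 3.5 points. The first row shows essentially no loss when the covariates carry no information.

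**4. Simulation with the three named measures.** Same rates and N, 2,500 runs per case, site-only against adjusted. The assumed odds ratios are for the higher intention level, an early first cigarette, and one SD of confidence.

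- 1.5, 0.75, 1.2: ratio of squared mean z = 1.012, worth 0.012 × 1350 ≈ 16 participants; power 82.7% to 83.1%.
- 2, 0.6, 1.4: ratio 1.028, worth about 38 participants; power 83.2% to 83.9%.
- 3, 0.5, 1.6: ratio 1.065, worth about 88 participants; power 81.1% to 83.6%.

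**5. Can the data carry the list?** Expected abstainers: 675 × 0.080 + 675 × 0.128 = 54.0 + 86.4 = 140.4. Arm (1), site (2), five-level stratum (4), and one term each for time to first cigarette, confidence and intention (3) make 10 coefficients, or about 14 events per coefficient.

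**The case against.** The strongest reply is that nothing here is wrong. Arm plus site is a valid, pre-named model, 1350 reproduces without covariates, and enrolment passed the target. That stands, and it limits the point to an efficiency improvement. The choice is nevertheless stated in the text, not left to an unseen document, and it can be improved with data already in hand.

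Four stronger readings are tempting but not supported:

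- *That these measures are strong predictors.* The article gives no prognostic strength for any of them, and eligibility cuts intention to two levels. Every odds ratio and R² above is an assumption. The largest gain in step 4 is also partly simulation noise in its level: its unadjusted power of 81.1% is lower than in the other two cases at the same rates and N.
- *That adjustment narrows the odds-ratio interval.* In logistic regression it does not. The target moves to a larger conditional odds ratio (1.69 to 1.78 in step 3) with a larger standard error, and the gain is in power. Narrower intervals appear for a standardised risk difference or risk ratio.
- *That the site-only result would be left biased by chance imbalance.* Randomisation is already stratified on daily cigarette consumption, which relates to dependence, and the type I error rate and interval allow for residual chance imbalance.
- *That secondary covariates will be picked after outcomes are seen, or by observed imbalance.* The Secondary outcomes section says neither. Its confounders are unnamed, but an article may leave that detail to a fuller plan.

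**Conclusion.** The point holds as a modest efficiency improvement to a valid model. Under assumed prognostic strength, adjusting for the baseline measures adds about 0.4 to 3.5 points of power at the planned N and rates, with essentially no loss if they prove uninformative. The size depends wholly on those assumptions. The gain in precision shows on the marginal scale, which is also the scale of the 4.8-point planning target. No error in the sample size, bias in the primary comparison or post hoc selection of covariates is shown. The article reports follow-up still in progress, so the list can be fixed before outcomes are analysed.

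**What to change.** Before outcome analysis, write into the analysis plan:

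1. One covariate list for the primary logistic model: site, the randomisation strata (daily cigarette consumption, admitting service, HIV), time to first cigarette, confidence and intention. State the coding of each.
2. A simple fixed rule for missing baseline values.
3. A standardised (marginal) risk difference with its confidence interval, reported beside the conditional odds ratio.
4. The site-only logistic model as a supporting analysis.
5. The same list in the secondary abstinence models, in place of the open-ended confounder wording. It need not extend to the counts of emergency visits and readmissions, because nothing in the article suggests that intention or confidence predicts those.

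The cost is analysis-plan wording and a standardisation step in the code. There is no new data collection and no change to sample size or trial conduct. The one real consequence is that the adjusted odds ratio is conditional and not directly comparable with the site-only one, which is why items 3 and 4 belong with item 1.

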#### Secondary outcomes

For all outcomes measured at 1, 3, and 6 months, cross-sectional analyses will be used to compare between study groups. Secondarily, a longitudinal analysis using Generalized Estimating Equations (GEE) techniques will be conducted to assess the overall impact of Sustained Care by including data from all follow-up times. Similar to the primary outcome, regression models will be used to compare treatment group adjusting for site and any important confounders; these will be logistic regression for dichotomized outcomes (e.g. self-reported abstinence, any counseling/medication use), and Poisson regression for the number of event outcomes (e.g. number of counseling contacts, number of emergency room visits, number of hospital readmissions). Survival analysis techniques will be used to analyze the duration-related outcome variables (self-reported duration of continuous abstinence and duration of post-discharge medication use). Kaplan-Meier curves will be used to estimate the median duration of tobacco abstinence and medication use. Cox proportional hazard models will examine intervention effects adjusting for potential confounding factors.

*Cost-effectiveness* will be assessed using cost per quit as the main outcome in order to compare our results with other published studies [22,34,35]. The incremental costs per quit are estimated as follows: (Total costs of Sustained Care – Total costs for Standard Care)/(Total successful quits at six months for Sustained Care – Total successful quits at six months for Standard Care) where successful quits are defined according to our primary outcome of 7-day point prevalence abstinence. The major costs tracked in the study are as follows: (1) initial counselor assessment pre-discharge, which includes counselor chart review, counseling, and medication recommendations; (2) Quit Coach medication assessment and cessation support post-discharge; (3) IVR service; and (4) medication costs, including dispensing and delivery. For both study arms, we will track the portion of counseling and medication costs paid for by participants out of pocket and/or by insurance.

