#### Access to smoking cessation telephone counseling support

An innovation of the HH2 study is the facilitation of real-time transfer from the automated call to a live telephone counselor in order to maximize treatment continuity at the time of need. This immediate transfer is made possible through coordination between the IVR provider, TelASK Technologies (Ottawa, Canada), and the telephone counseling provider, Alere Wellbeing Inc., (Seattle, WA) (Table 1). Alere offers its standard protocol of up to 5 proactive telephone counseling calls over 3 months to support a quit attempt [27]. The goal is to have a seamless link between IVR monitoring and request for telephone counseling support. Alere staff also provide smokers with NRT refills when these are due, thereby facilitating medication adherence.

Upon transfer from the IVR system to the quitline provider, the participant speaks to a registration agent who collects basic information and then routes the caller to a smoking cessation counselor (“Quit Coach”). The Quit Coach provides the following: (1) an introduction, presenting an overview of topics and the purpose of the call; (2) assessment of the participant’s smoking history, confidence and motivation to quit; (3) specific insight for the participant—summarizing the participant’s strengths, weaknesses, and barriers to quitting; (4) an action plan, which consists of setting a realistic quit date, brainstorming strategies to cope with urges, planning to rehearse coping skills, and addressing medication use, environmental factors, and social support; and (5) schedule for the next call, tailored to the participant’s quit date. The Quit Coach calls the participant for up to 4 additional counseling sessions. Call 2 is scheduled on or around the quit date and includes management of withdrawal symptoms, appropriate use of medications, strategies to maintain abstinence in high-risk situations, and early relapse prevention. Calls 3 through 5 focus on relapse prevention and addressing participant concerns and questions [28]. In addition, once registered with Alere, a participant can call in to speak with a Quit Coach directly at any time.

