#### Health care utilization

We will calculate the rate of all-cause re-hospitalizations, re-hospitalization for coronary heart disease, emergency room visits, and all-cause deaths over 6 months after the index hospitalization. Measures include (1) number of hospital readmissions, (2) length of stay in hospital, (3) number of emergency room visits, and (4) total number of hospitalizations and emergency room visits. An electronic health record tracking system automatically notifies research staff when a study participant has an emergency room visit or hospitalization at facilities in Partners Healthcare System, the integrated health care delivery system to which MGH and NSMC belong. At the end of the study, data on these events will be obtained from Partners billing data. At UPMC, information about hospital readmissions to UPMC-affiliated hospitals is obtained from chart review of participants’ electronic health records.

Information about hospitalizations and emergency room visits outside UPMC and Partner’s Healthcare System are obtained from participant surveys, by asking the questions “Since you were discharged from [hospital name] on [date] have you gone to the emergency room or stayed overnight at any hospital? This includes rehabilitation or skilled nursing facilities”. We request hospital name, type of visit (either ED, admission, inpatient rehab,) length of stay, and the hospitalization date. This is supplemented by requesting medical records of admissions to hospitals outside Partners HealthCare System and UPMC-affiliates.

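### Poisson regression is fixed for counselling contacts, emergency visits and readmissions with no provision for over-dispersion, which is expected here though not quantified

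*Protocol article*

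**What the plan says.** The Secondary outcomes part of the Data analysis section assigns a model family to each type of outcome. For counts it is "Poisson regression for the number of event outcomes (e.g. number of counseling contacts, number of emergency room visits, number of hospital readmissions". These models share a general rule: "regression models will be used to compare treatment group adjusting for site and any important confounders". The section does not mention over-dispersion, a variance estimator or an exposure term for the counts. It adds that, secondarily, "a longitudinal analysis using Generalized Estimating Equations (GEE) techniques will be conducted to assess the overall impact of Sustained Care"; no variance estimator is given there either.

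Two other sections describe how the counts arise. Under telephone counselling support: "Alere offers its standard protocol of up to 5 proactive telephone counseling calls over 3 months to support a quit attempt". A participant enters that series by asking for, or accepting, a transfer during an automated call, and once registered may also phone in at will. Standard Care participants get nothing further from the study after discharge. The Health care utilization section counts readmissions, emergency visits and their total, over a period described as "emergency room visits, and all-cause deaths over 6 months after the index hospitalization".

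**The concern.** A Poisson model sets the variance equal to the mean. That is doubtful for all three named counts.

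- **Counselling contacts.** One decision to accept a transfer can produce several calls, and declining leaves a zero for the study's own service. Zeros mixed with clusters push the variance above the mean unless nearly everyone takes up the service.
- **Readmissions and emergency visits.** The trial set out to recruit a medically and socially varied inpatient sample, including patients with substance use and HIV infection, from academic and community hospitals. When underlying rates differ between patients, the pooled count has a variance above its mean. Adjusting for site will not remove that.

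If the standard errors come from the Poisson likelihood, confidence intervals would be too narrow. A chance difference in readmissions or emergency visits could then be reported as an effect of Sustained Care on health-care use, and the abstract lists hospital readmissions among the trial's outcomes.

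**Working it through.** **1. The plan's own figure.** The only sample-size statement concerns the binary primary outcome: "A total sample of 1350 was planned to detect a difference of 4.8% (12.8% vs. 8.0%) in the primary outcome measure", "with 80% power and a 2-tailed type I error rate of .05". With p1 = 0.128, p2 = 0.080, mean 0.104 and difference 0.048:

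- Uncorrected: n = [1.960·√(2·0.104·0.896) + 0.842·√(0.128·0.872 + 0.080·0.920)]² / 0.048² = 633.7, so 634 per arm (1268 in total).
- With continuity correction: (633.7/4)·[1 + √(1 + 4/(633.7·0.048))]² = 674.7, so 675 per arm, 1350 in total.

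The stated 1350 is reproduced and this point does not touch it. Allocation is "in a 1:1 fashion using permuted blocks of 8", so 675 per arm is used below. The documents give no mean, variance or power for any count.

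**2. Effect of over-dispersion on the test.** Let φ = variance/mean, the same in both arms. The model-based Poisson standard error is the true one divided by √φ, so the two-sided rejection rate under no effect is 2·[1 − Φ(1.96/√φ)]. The values of φ are assumptions.

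| φ (assumed) | Model SE / true SE | Rejection at nominal 5% |
|---|---|---|
| 1.0 | 1.00 | 5.0% |
| 1.2 | 0.91 | 7.4% |
| 1.5 | 0.82 | 11.0% |
| 2.0 | 0.71 | 16.6% |
| 2.5 | 0.63 | 21.5% |
| 3.0 | 0.58 | 25.8% |
| 4.0 | 0.50 | 32.7% |

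Twice nominal needs φ of about 1.42, and three times nominal about 1.85.

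**3. Simulation check.** Gamma-Poisson counts, 675 per arm, no true effect, site-adjusted Poisson model, 1500 replicates per row:

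| φ | Model-based | Pearson-scaled | Sandwich |
|---|---|---|---|
| 1.0 | 4.1% | 3.9% | 3.9% |
| 1.3 | 8.3% | 4.9% | 5.0% |
| 1.5 | 12.4% | 6.6% | 6.7% |
| 2.0 | 18.3% | 5.5% | 5.5% |
| 2.6 | 22.8% | 5.5% | 5.6% |
| 4.0 | 33.6% | 5.7% | 5.7% |

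The simulation agrees with the formula within simulation error. In the over-dispersed rows, scaled or sandwich errors give about 5% to 7%.

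**4. What φ might be for counselling contacts in Sustained Care.** Assume a share q takes up counselling and that those who do have 1 to 5 contacts, equally likely. A user's count then has mean 3 and mean square 11. Over the whole arm the mean is 3q and the variance 11q − 9q², so φ = (11q − 9q²)/(3q) = 11/3 − 3q. The last column uses a distribution weighted to single contacts (50%, 20%, 15%, 10% and 5% for 1 to 5 contacts).

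| Uptake q (assumed) | φ, equally likely 1–5 | φ, mostly single contacts |
|---|---|---|
| 20% | 3.07 | 2.35 |
| 30% | 2.77 | 2.15 |
| 50% | 2.17 | 1.75 |
| 70% | 1.57 | 1.35 |
| 90% | 0.97 | 0.95 |

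Under the equally likely version, φ exceeds 1 for uptake below about 89% and exceeds 1.85 below about 61%. Over-dispersion is therefore expected over most of the range but not certain.

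**5. Readmissions and emergency visits.** Nothing in the documents allows φ to be computed. The case for φ > 1 is qualitative.

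**The case against.** The strongest reply is that this is a condensed article. One paragraph names model families for all secondary outcomes; it does not say that standard errors will be model-based, and a dispersion check, robust variance or offset may sit in an analysis plan that is not shown. This stands in part. Silence does not prove uncorrected errors, and Poisson regression with sandwich variance would be compatible with the published words. But the model family is fixed in the text, and following it with default standard errors would give the result above. The generalised estimating equations do not settle the matter, since they are only the secondary longitudinal analysis.

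Three stronger readings are tempting, and the documents do not support them.

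- **That the design forces over-dispersion and the error rate will be several times nominal.** No uptake or dispersion figure is given. The automated calls recommend a counsellor in many situations, and nicotine replacement refills run through the Quit Coach, so uptake could be high; near 90%, φ falls just below 1.
- **That counselling contacts carry a false-positive rate of about 24% (φ = 2.77 at 30% uptake).** The call package is supplied only in Sustained Care, so equal means are implausible and a rate under no difference has little meaning. The outcome also counts counselling from any source.
- **That the model assumes equal time at risk, with outside events known only from surveys.** The Data analysis section is silent on person-time, while the Health care utilization section speaks of a rate. In-system events come from tracking, billing data or chart review, and survey reports of outside events are supplemented by requests for medical records. A life expectancy under 1 year is an exclusion, which limits deaths.

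**Conclusion.** The point holds in conditional form. Poisson regression is the only model named for counts whose variance is expected to exceed the mean, and no provision is made for it. If model-based errors are used, the size of the problem depends wholly on φ, which has to be assumed. For φ between 1.2 and 4, the error rate for readmissions and emergency visits would be about 7% to 33% instead of 5%. Over the same range, intervals for any of the counts, including counselling contacts, would be about 91% to 50% of their proper width on the log scale. The step from φ to error rate is firm; the values of φ are not. The primary logistic analysis and the planned 1350 are unaffected, so this is a moderate correction to secondary analyses.

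**What to change.** State in the analysis plan that count outcomes will be analysed by Poisson regression with robust (sandwich) variance, or by negative binomial regression, adjusted for site and randomisation stratum. For readmissions, emergency visits and their total, include as offset the log of observed time, running to death or the end of ascertainment and at most 6 months. The robust variance or negative binomial model is what cures the dispersion problem. The stratum term brings the model into line with the allocation scheme, and the offset makes the utilisation analysis match the rate that the article says it will calculate. If the unseen analysis plan already contains this, confirming it closes the point.

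The change is one or two sentences, with no new data beyond dates of death and last ascertainment. The downside is somewhat wider intervals than default Poisson errors would have given.
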